# The effect of vitamin D and magnesium supplementation on clinical symptoms and serum inflammatory and oxidative stress markers in patients with COVID-19: a structured summary of a study protocol for a randomized controlled trial

**DOI:** 10.1186/s13063-023-07107-4

**Published:** 2023-02-06

**Keywords:** COVID-19, Clinical trial protocol, Vitamin D, Magnesium, Dietary supplements

## Abstract

**Objectives:**

This study aims to evaluate the effect of vitamin D and magnesium supplementation on clinical symptoms and serum inflammatory and oxidative stress markers in patients with COVID-19.

**Trial design:**

This study is a 4-arm randomized, double-blind, placebo-controlled clinical trial with a factorial design and the intervention period is 3 weeks.

**Participants:**

This study is conducted on COVID-19 patients admitted to the Shahid Mohammadi hospital in Bandar Abbas, Iran, who are eligible for inclusion in the study. Patients are included only if they meet all of the following criteria: (1) aged from 18 to 65 years old; (2) confirmation of COVID-19 by RT-PCR test; (3) completing informed consent; (4) passing less than 48 h since the patient's hospitalization; (5) no skin or gastrointestinal allergies due to taking multivitamin supplements, vitamin D, and magnesium; and (6) having more than 30 breaths per minute and less than 93% oxygen saturation in room air and sea level. Patients are excluded if they have any of the following conditions: (1) pregnancy or lactation; (2) taking a daily multivitamin or take a vitamin D or magnesium supplement in the last month; (3) participating in other clinical trials; (4) renal failure or dialysis, severe liver disease or cirrhosis; (5) known diagnosis of hypercalcemia; (6) discharging from the hospital less than 24 h after the start of the intervention; (7) history of kidney stones in the last year; (8) transfer the patient to the ICU; (9) baseline vitamin D levels above 80 ng/ml; (10) baseline magnesium levels above 2.6 mg/dl; and (11) unwillingness of the patient to continue the study.

**Intervention and comparator:**

Participants will be randomly allocated to one of the four following groups: (A) vitamin D (two 50,000 IU capsules at the beginning of the study, two 50,000 IU capsules on the 4th day, one 50,000 IU capsule on the 11th day, and one 50,000 IU capsule on the 17th day) and magnesium supplement (300 mg/day); (B) vitamin D capsule and magnesium placebo; (C) magnesium supplement and vitamin D placebo; and (D) vitamin D placebo and magnesium placebo.

**Main outcomes:**

The resolution of clinical symptoms (fever, dry cough, shortness of breath, headache, myalgia, oxygen saturation, and mortality rate) and interpretation of laboratory assays (CRP, MDA, TAC, WBC, neutrophils count, lymphocytes count, ratio of neutrophils to lymphocytes, levels of 25 hydroxyvitamin D and magnesium) will be assessed in the study groups.

**Randomization:**

A computer-generated block randomization list is used for randomization.

**Blinding (masking):**

Investigators and patients are blinded to group allocation and treatment. A double-blind design is achieved using matched placebos.

**Numbers to be randomized (sample size):**

A total of 104 eligible patients are randomized into four groups of 26 subjects (1:1:1:1 allocation ratio).

**Discussion:**

With the rapid prevalence of COVID-19 in recent years, more attention has been paid to effective dietary supplementation to improve clinical symptoms and biochemical parameters in these patients. To our knowledge, this is the first study to evaluate the effects of vitamin D supplementation in combination with magnesium or alone with respect to this infectious disease. The findings of the current RCT will provide evidence regarding the effectiveness of dietary supplementation strategies to improve COVID-19 outcomes.

**Trial status:**

Ethical approval of the first version of the study protocol was obtained from the medical ethics committee of Hormozgan University of Medical Sciences, Bandar Abbas, Iran on May 30, 2021 (IR.HUMS.REC.1400.085). Currently, the recruitment phase is ongoing since August 23, 2021, and is anticipated to be complete by the end of August 2022.

**Trial registration:**

The study protocol was registered in the Iranian Registry of Clinical Trials (https://www.irct.ir; IRCT20210702051763N1) on August 14, 2021. https://www.irct.ir/trial/57413

**Full protocol:**

The full protocol is attached as an additional file, accessible from the Trials website (Additional file 1). In the interest in expediting dissemination of this material, the familiar formatting has been eliminated; this letter serves as a summary of the key elements of the full protocol.

**Supplementary Information:**

The online version contains supplementary material available at 10.1186/s13063-023-07107-4.

## Introduction

A new coronavirus (SARS-CoV-2) infection commonly known as COVID-19 disease has become an epidemic in all world regions since November 2019 beginning in the city of Wuhan, China. It has become even more prevalent in the rest of the world than inside China, and the epidemic is still spreading [1]. This infection can mostly lead to severe acute upper and lower respiratory and gastrointestinal tract symptoms, especially in older people or those with chronic underlying diseases such as diabetes, coronary artery disease, and hypertension [1]. COVID-19 involves different organs and causes many complications because of the reduced immune system function [2].

One of the most important issues of this new infectious disease is investigating and determining the possible effects of nutrition and dietary supplementation in the prevention and treatment of disease [3]. It should be mention that a growing body of evidence supported the nutritional components in immune system enhancement [4]. Vitamin D and magnesium are among the essential nutrients that play important roles in the physiological functions and immune system [5].

Vitamin D deficiency is a worldwide concern that has been shown to be associated with increased risk for several diseases and clinical conditions [6, 7]. The effectiveness of vitamin D in the stimulation of innate immunity and modulation of acquired immunity has been known [8]. A meta-analysis also concluded that vitamin D supplementation is safe and associated with protective effects against acute respiratory tract infection [9]. On the other hand, Meltzer et al. reported a higher COVID-19 risk in individuals with vitamin D deficiency who were not sufficiently treated (deficit group: 21.6% vs. sufficient group: 12.2%) [10]. It has been suggested that considering the favorable effects of treating vitamin D deficiency on respiratory tract infections, during this pandemic period, the circulating 25-OH vitamin D should maintain at optimal levels (75–125 nmol/L) through taking vitamin D supplements [11]. However, it is stated that there is still a need for more research work to better understand the role of vitamin D in reducing disease severity and mortality [11].

Magnesium is an important mineral in the activation of a variety of enzymes and physiological functions in metabolic regulation, vasomotor tone, and muscle contraction [12]. Its supplementation is supported to play roles in the prevention or treatment of various types of diseases related to the respiratory system [12]. It has been suggested that magnesium also contributes to the antioxidant and anti-inflammatory effects on lung injury [13]. Magnesium and vitamin D could have a positive effect on inflammation and reduce cytokine production and coagulation cascade [14]. Subclinical magnesium deficiency has been reported to be associated with the debilitation of the immune system [14, 15]. Indeed, since the intracellular free magnesium regulates the cytotoxic functions of natural killer and cytotoxic T cells, the reduced intracellular free magnesium levels can lead to defective expression of programmed cell death in these immune cells [16].

In a cohort study among hospitalized patients with COVID-19 older than 50 years, supplementation with 1000 IU/day vitamin D, 150 mg/day magnesium, and 500 mcg/day vitamin B_12_ simultaneously was associated with less need for oxygen therapy and ventilation. Interestingly, those patients who did not receive this supplementation needed a 3.5-fold higher rate of oxygen therapy throughout hospitalization versus those who received the vitamin/mineral supplement (61.5% vs. 17.6%, *P* = 0.006) [17].

Considering that vitamin D and magnesium balance are required for optimal biological function, it is likely that vitamin D and magnesium have synergistic effects in COVID-19. To our knowledge, there is no previous clinical trial of vitamin D supplementation in combination with magnesium or alone with respect to this infectious disease. Therefore, we aim to conduct a randomized, double-blind, placebo-controlled clinical trial with a factorial design to evaluate the effect of vitamin D and magnesium supplementation on clinical symptoms, inflammatory markers, and oxidative stress in patients with COVID-19.

## Materials and methods

### Trial design

This study is a 4-arm randomized (1:1:1:1 allocation ratio), double-blind, placebo-controlled clinical trial with a factorial design and the intervention period is 3 weeks. This study aims to evaluate the effect of vitamin D and magnesium supplementation on clinical symptoms and serum inflammatory and oxidative stress markers in patients with COVID-19 admitted to the Shahid Mohammadi hospital in Bandar Abbas, Iran.

### Participants

Inclusion criteria:Age from 18 to 65 years oldConfirmation of COVID-19 by RT-PCR testCompleting informed consentPassing less than 48 h since the patient’s hospitalizationNo skin or gastrointestinal allergies due to taking multivitamin supplements, vitamin D, and magnesiumHaving more than 30 breaths per minute and less than 93% oxygen saturation in room air and sea level

Exclusion criteria:Pregnancy or lactationTaking a daily multivitamin or take a vitamin D or magnesium supplement in the last monthParticipating in other clinical trialsRenal failure or dialysis, severe liver disease or cirrhosisKnown diagnosis of hypercalcemiaDischarging from the hospital less than 24 h after the start of the interventionHistory of kidney stones in the last yearTransfer the patient to the ICUBaseline vitamin D levels above 80 ng/mlBaseline magnesium levels above 2.6 mg/dlUnwillingness of the patient to continue the study

Patients should not participate in another study at the same time but the routine treatment of COVID-19 in all groups is continued.

### Intervention and comparator

Participants will be randomly allocated to one of the four following groups: (A) vitamin D (two 50,000 IU capsules at the beginning of the study, two 50,000 IU capsules on the 4th day, one 50,000 IU capsule on the 11th day, and one 50,000 IU capsule on the 17th day) and magnesium supplement (300 mg/day); (B) vitamin D capsule and magnesium placebo; (C) magnesium supplement and vitamin D placebo; and (D) vitamin D placebo and magnesium placebo.

To ensure patient compliance with the assigned treatment, the subjects are monitored weekly by telephone and, if necessary, in-person visits. The compliance rate will be calculated according to the number of delivered and returned capsules by the following formula: number of capsules delivered − number of capsules returned/number of capsules delivered.

The criteria for discontinuation are any medical complications during supplementation or at the request of the patient. However, there is no possibility of harm to participants due to the type of dietary intervention. If the assigned intervention is discontinued for any reason, the patient has to be excluded from the study.

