### Main outcomes

The resolution of clinical symptoms and interpretation of laboratory assays will be assessed in the study groups.

Clinical symptoms:FeverDry coughShortness of breathHeadacheMyalgiaOxygen saturationMortality rate

Laboratory markers:C-reactive protein (CRP)Malondialdehyde (MDA)Total antioxidant capacity (TAC)White blood cell (WBC)Neutrophils countLymphocytes countThe ratio of neutrophils to lymphocytesLevels of 25 hydroxyvitamin D and magnesium

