### Statistical analysis

The Kolmogorov–Simonov test will be used to check the normality of variable distribution. One-way ANOVA and Bonferroni post hoc tests will be used to analyze the differences between groups.

The mixed linear model will be used to estimate the treatment effect and the possible confounding variables will be adjusted in the model. IBM SPSS version 22 will be used for statistical analysis. *P*-value ≤ 0.05 will be considered a significant level in all statistical tests. To handle protocol non-adherence, the intention-to-treat (ITT) principle will be used to analyze data based on the original treatment assignment of the patients. Variables will be expressed as mean ± standard error or 95% confidence interval. The research team will not conduct interim analyses to stop or extend the trial because of the low-risk nature of the nutritional intervention in the present study. Indeed, early detection of the study hypotheses is unlikely and early termination of the intervention is not supposed to have any additional protection for patients.

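### Exclusions applied after randomisation contradict the stated ITT analysis and, if carried out, would probably remove a large share of the deaths

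*Protocol article*

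**What the plan says.** **Exclusion on stopping.** The Intervention and comparator section states: "If the assigned intervention is discontinued for any reason, the patient has to be excluded from the study". It names the triggers just before: "The criteria for discontinuation are any medical complications during supplementation or at the request of the patient".

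**Exclusion list.** The Participants section, in both the abstract and the main text, includes:
- "discharging from the hospital less than 24 h after the start of the intervention"
- "transfer the patient to the ICU"
- "unwillingness of the patient to continue the study"

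The vitamin D and magnesium level criteria in the same list are expressly tied to baseline. These three are not.

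**Analysis.** For protocol non-adherence, the Statistical analysis section says "the intention-to-treat (ITT) principle will be used to analyze data based on the original treatment assignment of the patients".

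**Outcomes.** The Main outcomes section says: "The resolution of clinical symptoms and interpretation of laboratory assays will be assessed in the study groups". The items listed there include shortness of breath, oxygen saturation and "mortality rate". Data collection measures all outcomes at baseline and at three weeks. The article does not describe follow-up of excluded patients.

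**The concern.** Stopping the assigned supplement is the central form of non-adherence. For a patient who stops, one section keeps the patient in the assigned arm and another puts the patient out of the study. A team following the article cannot do both.

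The choice matters because the exclusions are not random. Medical complications and ICU transfer are part of the disease course and may depend on treatment. Patients enter with more than 30 breaths per minute and saturation below 93%, so deterioration on study is plausible. Removing those who deteriorate would leave a comparison of the patients who stayed on the ward and on supplement, and deaths after ICU transfer would drop out of the mortality comparison.

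**Working it through.** **1. The rules side by side**

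| Event | Possible before entry? | Exclusion rule | Statistical analysis section |
|---|---|---|---|
| Supplement stopped, any reason | No | Out of the study | Analysed as assigned |
| Discharge under 24 h after start of intervention | No | Exclusion criterion | Analysed as assigned |
| Unwilling to continue | No | Exclusion criterion | Analysed as assigned |
| ICU transfer | No time point given; worded as an event | Exclusion criterion | Analysed as assigned, if it occurs after entry |

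The first three rows conflict whichever way the fourth is read.

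**2. Numbers lost**

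From the Sample size section: 104 patients, 26 per group, dropout allowance 0.1, so 104 × 0.1 = 10.4 patients for all losses. The article gives no ICU rate. Assuming 10-30%, ICU transfer alone accounts for 104 × 0.10 = 10.4 to 104 × 0.30 = 31.2 patients. The allowance replaces numbers; it does not correct exclusion that depends on outcome.

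**3. Share of deaths removed (all rates assumed)**

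Share = p·d_ICU / [p·d_ICU + (1 − p)·d_ward], where p is the ICU transfer rate, d_ICU is death after transfer and d_ward is death without transfer. Deaths retained per 104 = 104·(1 − p)·d_ward. Each cell gives the share removed, then expected deaths per 104 before → after exclusion.

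| p | d_ICU | d_ward 2% | d_ward 5% |
|---|---|---|---|
| 10% | 30% | 62% (5.0 → 1.9) | 40% (7.8 → 4.7) |
| 10% | 50% | 74% (7.1 → 1.9) | 53% (9.9 → 4.7) |
| 20% | 30% | 79% (7.9 → 1.7) | 60% (10.4 → 4.2) |
| 20% | 50% | 86% (12.1 → 1.7) | 71% (14.6 → 4.2) |
| 30% | 30% | 87% (10.8 → 1.5) | 72% (13.0 → 3.6) |
| 30% | 50% | 91% (17.1 → 1.5) | 81% (19.2 → 3.6) |

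For example, 0.1 × 0.3 / (0.1 × 0.3 + 0.9 × 0.05) = 0.030/0.075 = 40%. The range is 40-91%, above half in 11 of 12 scenarios. This loss needs no difference between arms.

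**4. Bias in a week-3 marker (all inputs assumed)**

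Let severity S be standard normal on placebo, with ICU transfer above a cut-off c, and let the marker correlate r with S (higher is worse). Among those not transferred, the mean of S is −φ(c)/Φ(c) when S is standard normal.

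- 30% transferred: c = 0.524, mean = −0.348/0.70 = −0.497.
- 15% transferred: c = 1.036, mean = −0.233/0.85 = −0.274.

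*Mechanism A: fewer transfers on active, severity unchanged.* The true marker difference is 0. After exclusion it is r × (−0.274 + 0.497) = r × 0.222, against active: 0.067, 0.111 and 0.156 SD for r = 0.3, 0.5 and 0.7. Rate pairs 20/10 and 30/20 over the same r give 0.044-0.108 SD.

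*Mechanism B: fewer transfers because severity is lower, cut-off unchanged.* The required shift is 0.524 − 1.036 = −0.512. At r = 0.5 the true benefit is 0.5 × 0.512 = 0.256 SD. After exclusion the active mean is −0.512 − 0.274 = −0.786, so the observed benefit is 0.5 × (0.786 − 0.497) = 0.145 SD. For 20/10 the benefit goes from 0.220 to 0.142 SD, and for 30/20 from 0.159 to 0.085 SD.

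At 30/15 and r = 0.5 the displacement is 0.11 SD under both mechanisms: a false difference under A, a shrunken true benefit under B. With equal transfer rates this model gives no marker bias.

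**5. Scale**

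After those losses, two factorial margins of 52 keep 52 × 0.70 = 36.4 and 52 × 0.85 = 44.2 patients. The standard error of a difference is about √(1/36.4 + 1/44.2) = 0.22 SD. For two single arms (18.2 and 22.1) it is about 0.32 SD. A displacement of 0.11 SD is half a standard error or less.

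**The case against.** The strongest reply is that the article summarises a full protocol not shown here. Exclusion from the study may mean only that participation ends, and follow-up of those who stop may be described in the full protocol. ICU transfer has no time point and could be a screening criterion. These points rule out saying that the ITT analysis will certainly not be done. They do not remove the conflict: the article itself fixes both rules, and two listed criteria cannot be known at screening.

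A reader might infer four stronger things that the documents do not support:

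- *Most deaths are certainly removed.* No ICU or death rate is given. On assumed rates the share can be as low as 40%. A literal reading, under which any death before day 21 ends the intervention and so excludes the patient, is possible, but death is not among the named discontinuation triggers.
- *A supplement that prevents ICU transfer would look worse on every marker.* That reversal needs transfers to fall with no change in severity. If severity falls, a benefit shrinks but keeps its direction in the cases computed.
- *Every exclusion removes the sickest.* Discharge within 24 h more plausibly removes milder patients. It still breaks ITT.
- *All 104 could simply be analysed for everything.* Week-3 symptoms and blood cannot be obtained from patients who have died, or collected after consent is withdrawn.

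It is also fair to say that the marker bias is small against sampling error and rests on two assumed rates and an assumed correlation.

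**Conclusion.** The contradiction stands on the text alone and should be fixed. If the exclusions are applied, the analysis is not ITT and is conditioned on post-randomisation events related to outcome. The effect on mortality is the more serious: probably a large share of deaths is lost, 40-91% under the assumed rates. The marker bias is about 0.11 SD against a supplement that lowers transfers from 30% to 15% at r = 0.5, and its interpretation depends on the mechanism. That ICU transfer is a post-entry event is the natural reading but not an explicit statement.

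**What to change.** Reconcile the Participants and Intervention and comparator sections with the Statistical analysis section:

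1. Delete the sentence that excludes patients on discontinuation. State that stopping the supplement neither ends study participation nor removes the patient from analysis.
2. Mark which exclusion criteria apply only before randomisation. Record later ICU transfer, early discharge and withdrawal as events with reasons.
3. Where consent remains, follow every randomised patient to week 3, at least for vital status and ICU transfer. The weekly telephone contact already planned offers a route.
4. Analyse mortality for all randomised patients as assigned. Analyse symptoms and laboratory markers as assigned using all available data, and state how deaths are handled. Report ICU transfer or death by arm.

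The Trial status section expected recruitment to finish by the end of August 2022, and the article appeared in February 2023. If recruitment is complete, missed week-3 blood cannot be recovered. In that case recover vital status and ICU transfer from charts, report exclusions by arm and reason, and do not label an analysis that omits these patients ITT.

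No clinical stopping rule changes and no extra patients are needed. The cost is wording plus a status check for the patients now dropped, about 10-31 of 104 if ICU transfer is 10-30%.

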### Data collection

At baseline, general characteristics of patients including age, gender, medications used, and underlying chronic diseases are collected by investigators using a paper-based record system. All outcomes of interest (clinical symptoms and laboratory markers) are assessed at baseline and at the end of the intervention period (3 weeks later).

Data entry will be done by one of the blind research team members and a double check is performed by another blinded team member. Written informed consent is collected for each patient at the beginning of the study by investigators. Dietary supplements and biochemical tests are provided free of charge for participants to increase their willingness to participate in the study. Data protection was done by keeping the identity of the patients anonymous by excluding their names throughout the study.

After an overnight fast (10–12 h), 10 ml venous blood samples are taken from patients in the morning. First, 4 ml blood is collected in ETDA tube (1 mg/ml) and used for complete blood cell (CBC) count. The remaining 6 ml blood is allowed to clot for 45 min at room temperature; serum is then isolated by centrifugation at 3000 rpm for 10 min and stored at – 70 °C until analysis. Blood samples are collected and assayed by lab investigators that are blinded to the patient assignments.

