### Sample size

A total of 104 COVID-19 patients aged 18 to 65 admitted to the Shahid Mohammadi hospital in Bandar Abbas, Iran, who are eligible for the study are recruited. They are randomly divided into four groups of 26 subjects.

Based on the findings of the previous study [18], the sample size was calculated by the G*Power software, where the effect size for MDA variable was 0.68, alpha error probability was 0.05, power = 0.8, number of groups = 4, number of measurements = 2, and the assumed correlation among the repeated measures was 0.5. Then, taking into account the dropout rate of 0.1, the sample size in each group was estimated to be 26 patients.

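### Mandatory exclusion of every patient who stops the intervention conflicts with the promised intention-to-treat analysis and leaves those patients without an outcome

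*Protocol article*

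**What the plan says.** All places are in the protocol article.

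- **Intervention and comparator.** Grounds for stopping: "The criteria for discontinuation are any medical complications during supplementation or at the request of the patient". Consequence: "If the assigned intervention is discontinued for any reason, the patient has to be excluded from the study".
- **Statistical analysis.** For protocol non-adherence, the ITT "principle will be used to analyze data based on the original treatment assignment of the patients".
- **Data collection.** All outcomes "are assessed at baseline and at the end of the intervention period (3 weeks later"). No visit in between is described.
- **Participants (abstract, repeated in the methods).** The exclusion list includes discharge less than 24 h "after the start of the intervention", "transfer the patient to the ICU" and "unwillingness of the patient to continue the study".
- **Main outcomes.** Mortality rate and oxygen saturation are both listed.
- **Sample size.** 26 per group, 104 in total, "taking into account the dropout rate of 0.1".

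No sentence says that excluded patients are still followed or analysed.

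**The concern.** Stopping the assigned treatment is the most complete form of non-adherence. ITT is adopted to deal with non-adherence, yet the article makes this form of it a mandatory ground for exclusion. Two teams working from the same text could analyse different patients: all 104 as randomised, or only those who did not stop.

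The removal may also be selective. Medical complications are a named reason for stopping and may well be related to outcome. Patients enter with more than 30 breaths per minute and oxygen saturation below 93%, so later ICU transfer is plausible. If transfer leads to removal, mortality is the outcome most exposed, because the patients removed are those most likely to die. For any outcome, if the removed patients do worse than the rest and one arm loses more of them, the comparison favours the arm that lost more.

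**Working it through.** **1. The two rules side by side.** ITT by original assignment means 104 patients, 26 per arm. The exclusion rule means 104 minus everyone who stopped. Two readings might reconcile them:

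- *Excluded means only taken off treatment.* The text says the study, not the treatment. Even if the patient stays nominally in the analysis set, there is no value after baseline. A mixed model given only a baseline value gains no outcome from that patient.
- *ITT covers only patients who stay but take fewer capsules.* The article does not say so, and an analysis that omits those who stop is not ITT.

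**2. Timing of the listed exclusions.** Early discharge is counted from the start of the intervention, and unwillingness to continue presupposes participation. Both act after enrolment. ICU transfer has no timing; it can be read as a screening criterion or as a later removal.

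**3. Planned losses.** 0.1 × 104 = 10.4 patients, or 0.1 × 26 = 2.6 per arm, leaving 26 × 0.9 = 23.4. The size of 26 already allows for this (23 / 0.9 = 25.6, rounded up to 26), so at that rate the issue is bias and not power. The 10% is a general dropout allowance. The article gives no rate of stopping for complications.

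**4. Size of a possible bias (illustration).** Assumptions: no true effect; three patients in each arm of 26 are d SD worse than the rest of their arm; these are the ones at risk of removal. The document gives neither d nor the split of losses, so a range is shown.

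If all three are removed from one arm and m remain among n' patients in the other, the bias is (m / n') × d.

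| Losses | Factor | d = 0.5 | d = 1 | d = 1.5 | d = 2 |
|---|---|---|---|---|---|
| 3 v 3 | 0 | 0 | 0 | 0 | 0 |
| 3 v 2 | 1/24 | 0.02 | 0.04 | 0.06 | 0.08 |
| 3 v 1 | 2/25 | 0.04 | 0.08 | 0.12 | 0.16 |
| 3 v 0 | 3/26 | 0.06 | 0.12 | 0.17 | 0.23 |

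The standard error of a 26 v 26 difference is √(2/26) = 0.277 SD, so 3 v 0 amounts to 0.058/0.277 = 0.21 up to 0.231/0.277 = 0.83 standard errors.

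**5. Effect on the test, 3 v 0.** Simulated two-sample t-test, 23 patients against 26 that include the three worse ones:

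- Unadjusted two-sided 5%: rejection in about 5.3 / 6.0 / 7.3 / 8.6% of trials for d = 0.5 / 1 / 1.5 / 2.
- Bonferroni for six pairwise comparisons (0.05/6 = 0.8% nominal): about 0.9% at d = 0.5, rising to 1.7% at d = 2.

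**6. Pooled contrast.** If the mixed model compares one factor at 52 v 52 (the article does not state the contrast), the standard error is √(2/52) = 0.196 SD. Losing 5 v 0 gives (5/52) × d = 0.05 / 0.10 / 0.14 / 0.19 SD.

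**The case against.** **The rules can be reconciled.** Compliance is measured by capsule count, stopping is treated as exit, and 10% dropout is budgeted. On that view poor compliers stay in their arm and those who stop are dropouts. The article also summarises a full protocol that is not shown. This makes the point a conflict of wording that the full protocol may resolve. It does not remove it: both rules are stated, the exclusion is mandatory and without exception, and the reconciled analysis would carry the wrong name.

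**Blinding protects against one-sided loss.** Matched placebos mean that decisions to stop are made without knowledge of the arm. This stands. It makes unequal loss less likely, but arms may still differ if a supplement itself affects complications or deterioration, or by chance with about 2.6 losses per arm.

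**Baseline adjustment would reduce the bias.** If removed patients are equally worse at baseline (an assumption) and the correlation is 0.5 as in the Sample size section, adjustment leaves d × (1 − 0.5), about half. This stands as a partial remedy only.

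**Stronger readings that a reader might infer.**

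- *All three exclusions remove randomised patients.* The text supports this for two; the timing of ICU transfer is not stated.
- *The false-positive rate is badly inflated.* A noncentral t calculation with SD 1 in both arms gives 5.4 / 6.8 / 9.1 / 12.4%. It ignores the extra spread in the arm that keeps its worse patients, and the planned post hoc tests are Bonferroni-adjusted.

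**Conclusion.** The conflict holds on the text alone. If the exclusion sentence is followed, patients who stop have no week-3 outcome and the analysis is not the ITT analysis that the article states. This affects the analysis population of every outcome measured at week 3.

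Bias is possible but not shown. It needs losses that differ between arms and are related to outcome. Under the assumed range it runs from zero (equal and alike losses) to 0.23 SD (3 v 0, removed patients 2 SD worse), with at most a modest rise in false positives. The larger values need one-sided loss together with patients 1.5 to 2 SD worse. Mortality is the outcome most exposed if ICU transfer is applied after randomisation; the article gives no rates from which to size that. A reader should not conclude that the trial's comparisons are biased, only that the plan leaves an avoidable route to bias open. The point should be corrected.

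**What to change.** 1. Replace the exclusion sentence under Intervention and comparator with: *Patients who discontinue stop the supplement, are followed to week 3 where they agree, and stay in the ITT analysis in their assigned arm; numbers and reasons are reported by arm.*
2. Apply the same rule to ICU transfer, early discharge and unwillingness to continue when they occur after randomisation. Keep the Participants list for eligibility before randomisation.
3. Record vital status at week 3 for all randomised patients where possible.

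**Cost.** Wording changes in two sections and week-3 follow-up of about 10 patients at the planned dropout. Weekly telephone contact, with visits if needed, is already planned. Some patients will refuse; they should be counted by arm with reasons. Following even half of those who stop would roughly halve the 3 v 0 figures, to about 0.03 to 0.12 SD.

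**If recruitment has closed.** The article appeared in February 2023 and describes recruitment as ongoing, with completion expected by the end of August 2022, so the status is unclear. If recruitment is over, week-3 values of patients already excluded are probably lost. Exclusions can still be reported by arm with reasons from the allocation list numbered 1 to 104, and the analysis should then not be called full ITT.
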